### 2.11. Ethics and Dissemination

#### 2.11.1. Research Ethics Approval

This trial and all its associated forms and resources, have been approved by the National Healthcare Group Domain Specific Review Board (DSRB) in Singapore (2015/00611-Park Prescription Trial).

#### 2.11.3. Dissemination Policy

The research data will be compiled into a poster that may be used for conferences (both local and overseas). The research data will also be compiled and be written into a paper that will be sent for publishing in a peer-reviewed journal. In addition, we intend to share the key findings on the NParks website and on other relevant public forums and/or (inter)national newsletters. The content and type of media will always be agreed on among the organizations collaborating to conduct the trial.

## 4. Discussion

There is increasing interest in the health benefits of parks and other urban green spaces since epidemiological evidence suggests that exposure to green spaces in urban environments is associated with physical and mental health benefits [10,11,12,32]. A systematic review of the impact of interventions to promote physical activity in urban green space identified 12 studies with a control comparison and only one of these was an RCT [13]. Whilst seven of the twelve studies achieved positive impacts on physical activity and park usage, the single RCT the review identified was the only study that was assessed as being at low risk of bias [33].

The Park Prescription Trial is prospective, includes a control group, is randomized, incorporates an objective physical activity measure and is hypothesized to increase the utilization of urban green spaces. This RCT will evaluate the effectiveness of the Park Prescription intervention for increasing health-enhancing moderate-to-vigorous physical activity. It will also assess impacts on health behaviors including park use, whilst incorporating an assessment of mental wellbeing and physical health. Since there are no known RCTs of this novel approach to promoting health and well-being by prescribing physical activity in parks, this trial will make a significant contribution to physical activity intervention research and research into the health benefits of urban green spaces.

This study has several strengths, including a sample size that has been calculated to ensure adequate statistical power to detect the main outcome measure. Objective and valid data collection methods have been used for most of the outcome measures. A six-month follow-up will determine if the changes made during the intervention can be maintained. Since it is an effectiveness trial conducted in a community setting, it is likely to be more reproducible than an intensively-resourced efficacy study, which in turn increases the chances of the intervention being appropriate for scaling up to benefit larger segments of the population [34,35]. To aid this process of potential translation of this research for broader adoption there is also a complementary process evaluation which will explore implementation issues (reach, adoption, fidelity, satisfaction) as well as assess which aspects of the program may contribute to potential impacts (i.e., why the program achieved the results it achieved) using both quantitative and qualitative methods. Finally, the development of the intervention involved formative research and elements of this were informed by the PRECEDE-PROCEED theoretical model [36].

There are some risks and limitations associated with the trial. Community trials tend to be susceptible to loss to follow-up amongst participants. For this reason, intensive follow-up strategies were implemented and intention-to-treat analysis will be performed to reduce potential biases this may introduce. An intervention of this duration and intensity may not be expected to achieve large impacts on the chosen physical health indicators which include objectively-measured anthropometric, blood biochemical and blood pressure measures. However, these measures were part of existing health screenings that participants already had at baseline so there was an opportunity to assess potential impacts with only one additional measurement point.

## 5. Conclusions

Park Prescription is a novel approach to promoting participation in physical activity and exposure to urban green space. Therefore, a rigorous approach to evaluation of the Park Prescription Intervention was warranted. If found to be effective, health systems could translate the Park Prescription concept into broader use in primary care settings since it is relatively simple to implement. In the Singapore context, this intervention could benefit a large segment of the population if it were linked with existing screening programs which are offered free to all Singaporeans over 40 years of age.

## Figures and Tables

**Figure 1 ijerph-15-01154-f001:**
[figure not shown]
Flow of participants. ^a^ Physical Activity (PA) accelerometer refers to the instrument used to measure the main outcome measure.

**Table 1 ijerph-15-01154-t001:** Intervention components and intervention delivery timing.

Component	Description	Delivery Timing
Counselling	Face-to-face physical activity and park use counselling.	Commencement
Park Prescription	Participants completed a sheet with a trained study team member. The prescription section of the participant’s sheet outlined a goal they committed to which specified the frequency, intensity, time and location of exercise in parks. The study team retained a separate sheet with an assessment of the participant’s baseline activity level—low, moderate or active.	Commencement
Materials	Participants received two brochures: one developed for the Trial provided information on the main parks in the northern part of Singapore and their features, including walking trails (with time needed to complete them) and fitness corners. The other was a general brochure from the Singapore National Parks Board containing a map and information on the Northern Explorer Loop (a series of parks in Singapore’s north connected by a network of walking and cycling paths). A planning sheet, where participants filled in the types of activities they aimed to do each week over the trial period, also included information and examples.	Commencement
Follow-up counselling	Brief phone call counselling by a trained study team member. The counselling assessed progress towards set goals and included modification of those goals if necessary.	Three months
Group exercise	Structured exercise program delivered in parks by a trained group exercise instructor. To encourage attendance, participants received mobile text message reminders prior to each weekly exercise session.	Weekly over six months.

**Table 2 ijerph-15-01154-t002:** Outcome measures and instruments for data collection at each time point.

Primary Outcome	Measurement	Instrument	V0	V1	V2
MVPA	Time spent in activity of moderate to vigorous intensity	Accelerometer			X
**Secondary outcome**					
Physical activity	Total physical activity volume ^a^	Accelerometer			X
Light and sedentary activity	Time spent in light and sedentary activity	Accelerometer			X
Physical activity	Frequency, intensity, time and type	Self-administered questionnaire—GPAQ	X	X	X
Sedentary activity	Time spent sitting	Self-administered questionnaire—IPAQ	X	X	X
Park usage	Time spent in parks last month, physical activity time in parks on a typical month.	Self-administered questionnaire	X	X	X
Mental wellbeing	Wellness	Self-administered questionnaire—SF-12, K10, WHO5, WHOQoL-BREF ^b^	X		X
Anthropometry	BMI **^c^**—weight in kilograms divided by height in meters squared	BMI machine	X		X
Biochemistry	Blood lipids, fasting blood glucose	Blood samples	X		X
Blood pressure	Systolic and diastolic	Dinamap blood pressure monitor	X		X
**Process indicator ^d^**					
Motivation to exercise	Social support for physical activity, reasons to engage, physical activity knowledge	Self-administered questionnaire—BREQ-2		X	
Attitudes and behaviors	Perceived changes in participants’ attitudes and behaviors towards physical activity and park use, intention to continue group exercise	Self-administered questionnaire.			X
Satisfaction with and quality of program	Satisfaction with and quality of prescription sheet and parks brochure	Self-administered questionnaire		X	
	Satisfaction with and quality of physical activity planning sheet	Self-administered questionnaire		X	
	Satisfaction with and quality of phone counselling	Self-administered questionnaire			X
	Satisfaction with and quality of program overall	Self-administered questionnaire			X

V0 = Baseline, V1 = 3-month mid-intervention follow-up, V2 = 6-month follow-up at completion of the intervention. GPAQ Global Physical Activity Questionnaire (sections on work, transportation and recreational activities); IPAQ International Physical Activity Questionnaire, Part 5: Time Spent Sitting, item 26 and 27; SF-12, 12 item short-form survey, item 1; K10 Kessler Psychological Distress Scale; WHO5 WHO (Five) Well-being Index; WHOQoL-BREF WHO Quality of Life Short Form; BREQ-2 Exercise Regulation Questionnaire. ^a^ We use Euclidean Norm Minus One (ENMO) as the ‘total volume’ measure. It reflects ‘average acceleration’ in gravitational units (mg). [28,29]. ^b^ WHOQoL-BREF administered only at 6-month follow-up. **^c^ Body Mass Index (BMI). ^d^** Process indicators only administered to intervention group.

**Table 3 ijerph-15-01154-t003:** Outcome measures, their definitions and methods for evaluating the hypotheses.

Outcome	Hypothesis	Definition	Analysis
(1) Primary			
Time spent on MVPA ^a^—objective measure	Improvement in MVPA in intervention group as compared to control group at six months	Time spent on MVPA in minutes per week as measured by the accelerometer	*t*-test. Linear regression
(2) Secondary			
a. Health behaviors	Improvement in health behaviors in intervention group as compared to control group at six months		
Total volume of physical activity		Total activity volume as measured by the accelerometer ^b^	*t*-test. Linear regression
Time spent on light and sedentary activity		Time spent per week on light and sedentary physical activity as measured by the accelerometer	*t*-test. Linear regression
Time spent on MVPA—subjective measure		Self-reported time (minutes) per week spent on MVPA as recorded in questionnaire	*t*-test. Linear regression
Time spent in parks; time spent being physically active in parks		Self-reported time (minutes) in parks in the past month; and time spent engaging in physical activity in parks in a typical month as recorded in the questionnaire	*t*-test. Linear regression
Recreational MVPA time		Self-reported time (minutes) per week spent on recreational activity as measured by GPAQ^a^	*t*-test. Linear regression
Sitting time		Self-reported time (minutes) per week spent sitting as measured by IPAQ ^a^	*t*-test. Linear regression
b. Mental wellbeing	Improvement in mental wellbeing in intervention group as compared to control group at six months		
Mental wellbeing		Self-reported mental wellbeing as measured by SF-12 (1-item, general health), K-10, WHO5 and WHOQOL-BREF^a^	*t*-test. Linear regression. Logistic regression
c. Physical health	Improvement in physical health in intervention group as compared to control group at six months		
Body Mass Index (BMI)		Weight in kg divided by height squared in m measured by BMI machine.	*t*-test. Linear regression
Fasting blood glucose		Fasting blood glucose in mmol/L. Laboratory assessment	*t*-test. Linear regression
Systolic and diastolic blood pressure		Systolic and diastolic blood pressure in mmHG measured by a Dinamap blood pressure monitor	*t*-test. Linear regression

^a^ Abbreviations: MVPA, moderate-to-vigorous physical activity; GPAQ, Global Physical Activity Questionnaire; IPAQ, International Physical Activity Questionnaire. SF-12, 12 item short-form survey; K10, Kessler Psychological Distress Scale; WHO5, WHO (Five) Well-being Index; WHOQoL-BREF, WHO Quality of Life Short Form; BREQ-2, Exercise Regulation Questionnaire.^b^ We use Euclidean Norm Minus One (ENMO) as the ‘total volume’ measure. It reflects ‘average acceleration’ in gravitational units (mg) [28,29].

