#### 2.5.2. Secondary Outcomes

Secondary outcome measures are defined as the differences between the mean values in the intervention and the control groups at six months follow-up in health behaviors, mental wellbeing and physical health.

Measures for health behaviors related to physical activity include the total volume of activity reflecting average acceleration in gravitational units (mg), time spent in light intensity physical activity and sedentary activity measured by accelerometer, as well as recreational activity time per week, subjectively-measured total MVPA time per week and sedentary time per week assessed by self-administered questionnaire. The physical activity questions come from the previously validated WHO Global Physical Activity Questionnaire [22]. The questions on sedentary time come from the validated International Physical Activity Questionnaire [23]. Self-reported time spent in parks in the past month and time spent doing physical activity in parks in the past month were also included in the self-administered questionnaire at baseline, three months and six months follow-up.

The secondary outcome measures for mental wellbeing include the difference in self-reported quality of life and mental wellbeing between the intervention group and the control group at six months follow-up. This was measured by previously validated survey questions including the general health item from the SF-12, K-10, WHO5 and the WHOQOL-BREF [24,25,26,27]. The physical health measures are objectively-measured Body Mass Index (BMI), fasting blood glucose levels as well as systolic and diastolic blood pressure, as assessed prior to baseline and during the health screening visit at six months follow-up.

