#### 2.10.3. Statistical Analysis

For demographic variables of the intervention and control groups at baseline, descriptive statistics will be presented using mean and standard deviation for variables that are normally distributed and median and interquartile range for skewed continuous variables and proportion for categorical variables. Table 3 provides an overview of all primary and secondary outcome measures, their definitions and the methods to be used for evaluating the respective hypotheses.

For the continuous primary outcome of MVPA as well as continuous secondary outcomes based on health behavior, mental health and physical health measures at the six-month follow-up, the mean difference between the intervention and the control groups will first be evaluated using t-tests. Further adjustment for respective baseline values of the outcome variables (where available) of the individual will be made via multiple linear regression analysis. For accelerometer related outcomes where no baseline value is available, adjustment for total self-reported MVPA of the individual will be made via multiple linear regression analysis. For categorical outcomes at 6-months (e.g., depression/anxiety levels from K10) logistic regression will be conducted adjusting for the same covariates.

Subgroup analysis based on the report of engagement in physical activity in parks will be performed to investigate the effect of the intervention on the primary and secondary outcomes.

Up-to-date versions of R (Auckland, New Zealand) and STATA (Texas, TX, USA) will be used to conduct the analysis. All evaluations will be made based on intention to treat, assuming a two-sided test at the 5% level of significance. Effect sizes and 95% confidence intervals will also be reported for the respective outcome measures.

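### WHOQOL-BREF has no baseline and no substitute covariate, so it is the one non-accelerometer outcome in Table 3 compared unadjusted, although related wellbeing measures are held at baseline

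*Protocol article*

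**What the plan says.** Section 2.5.2 and Table 3 make WHOQOL-BREF a secondary outcome. Section 2.5.2 sets the comparison as self-reported "quality of life and mental wellbeing between the intervention group and the control group at six months follow-up". Table 3 puts it in one row with three other instruments, "Self-reported mental wellbeing as measured by SF-12 (1-item, general health), K-10, WHO5 and WHOQOL-BREF", and lists t-test, linear regression and logistic regression for that row as a whole.

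Table 2 also gives the four instruments a single row, "Self-administered questionnaire—SF-12, K10, WHO5, WHOQoL-BREF", marked at V0 and V2. Marker b sits on WHOQoL-BREF alone, and its footnote reads "WHOQoL-BREF administered only at 6-month follow-up".

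Section 2.10.3 sets the analysis in three steps:

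- For continuous outcomes, "the mean difference between the intervention and the control groups will first be evaluated using t-tests".
- Then: "Further adjustment for respective baseline values of the outcome variables (where available) of the individual will be made via multiple linear regression analysis".
- A stand-in is named for one class of outcome only: "For accelerometer related outcomes where no baseline value is available, adjustment for total self-reported MVPA of the individual will be made".

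**The concern.** The article recognises that some outcomes have no baseline and chooses a proxy for them, but words that rule for accelerometer outcomes only. WHOQOL-BREF is in the same position and is left out. An analyst following the text would have no covariate for it, even though three related measures of the same participants' wellbeing are held from V0.

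Two things are at stake, both for this one outcome. The first is precision: a covariate that predicts the outcome narrows the confidence interval at no cost in participants. The second is protection against a chance difference in baseline wellbeing between the arms. The other non-accelerometer outcomes in Table 3 can be corrected for such a difference through their own baselines.

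**Working it through.** **1. Is WHOQOL-BREF the only outcome between the rules?** Tables 2 and 3 set side by side:

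| Outcome | Own baseline (V0) | Covariate under Section 2.10.3 |
|---|---|---|
| Accelerometer MVPA, total volume, light and sedentary time | No | Self-reported MVPA |
| GPAQ measures, IPAQ sitting time, park time | Yes | Own baseline |
| SF-12 item, K10, WHO-5 | Yes | Own baseline |
| BMI, fasting glucose, blood pressure | Yes | Own baseline |
| WHOQOL-BREF | No (footnote b) | None named |

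It is the only one.

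**2. What does a regression without a covariate add?** The model is outcome = a + b × group. The least-squares estimate of b is the difference between the two means, and its test is the equal-variance t-test. For this outcome the regression would therefore duplicate the first analysis.

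**3. Are the proposed covariates measured before randomisation?** Table 2 marks SF-12, K10 and WHO-5 at V0. Section 2.9 says envelopes were opened after the baseline assessment was complete. So they are.

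**4. The article's own sample size.** Inputs from Section 2.6 are a difference of 30, SD 60, alpha 0.05 and 80% power; the two-sided test is from Section 2.10.3. The standardised difference is 30/60 = 0.5. The two-sample t-test needs 63.8, so 64 per group, and 64/(1 − 0.20) = 80 per group, 160 in total. The stated figures reproduce and are not in dispute. They concern MVPA; the article gives no effect size or power for WHOQOL-BREF.

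**5. Size of the gain from adjustment.** Let r be the joint (multiple) correlation of the three V0 measures with six-month WHOQOL-BREF. The article does not give r; 0.4 to 0.6 is assumed. Adjustment multiplies residual variance by (1 − r²), so the standardised difference d becomes d/√(1 − r²). Take n = 64 per arm and, for illustration, the d that gives 65% unadjusted power, which is 0.418:

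| r | Variance reduction r² | √(1 − r²) | d/√(1 − r²) | Power |
|---|---|---|---|---|
| 0 | 0% | 1.000 | 0.418 | 65% |
| 0.4 | 16% | 0.917 | 0.456 | 72.5% |
| 0.5 | 25% | 0.866 | 0.482 | 77.3% |
| 0.6 | 36% | 0.800 | 0.522 | 83.4% |

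Over a wider range of r, 0.3 to 0.7, the variance reduction is 9% to 49%. A 0.5 SD difference, with 80% power unadjusted, would have 84% to 98%. Three covariates take 3 of 126 degrees of freedom, which is negligible here.

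**6. Chance imbalance.** With 64 per arm, the standard error of a baseline difference in SD units is √(2/64) = 0.177. A difference of 0.25 SD or more in either direction is 0.25/0.177 = 1.41 standard errors, a probability of about 16%. At r = 0.5 it would move the unadjusted comparison by 0.5 × 0.25 = 0.125 SD.

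**The case against.** The strongest reply is that the plan is already complete for this outcome. The where-available clause means that, with no baseline, the t-test stands as the analysis. It can be carried out, and under randomisation it is unbiased. That is correct, and it is why this is an improvement to make and not an error in the result.

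A second reply is that Table 3 lists its methods for a row of four instruments, so it need not promise a linear regression for WHOQOL-BREF in particular. That also stands; the duplication in step 2 arises only if the row is read as applying to each instrument.

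A third is that covariate detail belongs in a full protocol or analysis plan that is not shown. This has some force, and such a document may name a covariate. But Section 2.10.3 is not silent on missing baselines. It fixes a substitute rule and confines it to accelerometer outcomes, so a plan that followed the text would carry the gap forward.

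Finally, the harm is limited: WHO-5, K10 and the SF-12 item cover related ground and are each adjusted, so a baseline imbalance in wellbeing would show there. That is true, but seeing an imbalance does not remove its effect from the WHOQOL-BREF estimate.

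A reader might also infer that Table 2 contradicts itself by marking WHOQOL-BREF at V0. It does not. The marks belong to the shared row, and the footnote marker on this instrument is an ordinary stated exception. Nothing else in the article says that it was collected at baseline.

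**Conclusion.** The point holds as a minor one. Followed as written, Section 2.10.3 leaves WHOQOL-BREF as the only non-accelerometer outcome in Table 3 without baseline adjustment, while suitable baseline measures are already held. The loss is one of precision and of protection against chance imbalance, in a single secondary outcome.

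The power gain from 65% to about 73–83% rests on an assumed joint correlation of 0.4 to 0.6 and on a 65% starting point chosen for illustration; neither is in the article. The 64 per arm is the planned evaluable number, not an observed count. The figures show what adjustment could bring and do not measure what this trial loses.

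It would be wrong to infer that the WHOQOL-BREF comparison is biased, or that the primary analysis or sample size is affected. Allocation is randomised, and neither of the latter depends on this questionnaire.

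**What to change.** Extend the substitute-covariate rule in Section 2.10.3 by one sentence: the WHOQOL-BREF linear regression adjusts for V0 WHO-5, V0 K10 and the V0 SF-12 general health item. Fix this before the six-month data are examined by arm, since staff are not blinded to allocation and a covariate chosen later would be open to question. If the investigators prefer no adjustment, they should state that WHOQOL-BREF is analysed by t-test alone.

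The cost is that one sentence; the covariates are already collected. Giving WHOQOL-BREF its own row in Table 2, marked at V2 only, would read more clearly but is optional and editorial.
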